# The role of cytoreductive nephrectomy in metastatic renal cell carcinoma in immune-oncology era (SEVURO-CN): study protocol for a multi-center, prospective, randomized trial

**DOI:** 10.1186/s13063-024-08234-2

**Published:** 2024-07-03

**Keywords:** Renal cell carcinoma, Cytoreductive nephrectomy, Ipilimumab, Nivolumab, Immune checkpoint inhibitors, Kidney neoplasms, Prospective studies

## Abstract

**Background:**

The role of cytoreductive nephrectomy (CN) in the treatment of metastatic renal cell carcinoma (mRCC) remains unclear in the immuno-oncology (IO) era. The results of two randomized trials, CARMENA and SURTIME, questioned the role and timing of CN. However, despite the latest advances in the systemic treatment of mRCC, previous trials have only used targeted therapy, and no studies have fully investigated the role of CN in immune checkpoint inhibitor (CPI) settings, and there is an urgent need for future studies to better define the role and timing of CN.

**Methods:**

This study is an open-label, multi-center, parallel, prospective, randomized, interventional clinical study to evaluate the efficacy of CN in combination with CPIs in mRCC patients with International mRCC Database Consortium (IMDC) intermediate- and poor-risk. Synchronous mRCC patients with ≤ 3 IMDC risk features will be randomly allocated to three groups (1, upfront CN; 2, deferred CN; and 3, systemic therapy [ST] only). For ST, the nivolumab plus ipilimumab combination regimen, one of the standard regimens for intermediate- and poor-risk mRCC, is chosen. The primary endpoint is overall survival. The secondary endpoints are progression-free survival, objective response rate, number of participants with treatment-related adverse events, and number of participants with surgical morbidity. We will analyze the genetic mutation profiles of the tumor tissue, circulating tumor DNA, urine tumor DNA, and tumor-infiltrating lymphocytes. The gut and urine microbial communities will be analyzed. The study will begin in 2022 and will enroll 55 patients.

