### Sample size justification

Two prospective RCTs, PROBE (NCT04510597) and NORDICSUN (NCT03977571), are currently ongoing, but do not include an upfront CN arm. We determined the sample size based on the most recent real-world data that analyzed the intermediate/high risk group of mRCC patients stratified into upfront CN, deferred CN, and systemic treatment group [17]. To determine the required sample size for the study, we utilized two calculators for two-group survival analysis [18]. For Calculator 1, with a two-tailed alpha level (*α*) set at 0.05 and a beta level (*β*) of 0.2, along with a proportion of subjects in Group 1 (upfront and deferred CN) of 0.66 and a proportion in Group 0 (ICIs only) of 0.34, the relative hazard was set at 0.37. The calculated number of events needed to achieve 80% power was 35. For Calculator 2, with the total number of events set at 35, and assuming a baseline event rate of 0.53 and a median survival time in Group 0 (ICIs only) of 1.3 years, along with a censoring rate of 0.1 and a planned average length of follow-up of 5 years, the sample sizes required for each group were determined. Therefore, a total of 57 subjects were needed for the study.

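### The abstract gives an enrolment target of 55, but the sample size section derives 57 and its inputs reproduce 57; the effect on power is small

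*Protocol article*

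**What the plan says.** The Methods paragraph of the abstract states: "The study will begin in 2022 and will enroll 55 patients".

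The Sample size justification works in two steps. The first finds the number of events, "with a two-tailed alpha level (*α*) set at 0.05" and "a beta level (*β*) of 0.2", with a "proportion of subjects in Group 1 (upfront and deferred CN) of 0.66", "a proportion in Group 0 (ICIs only) of 0.34", and a further input: "the relative hazard was set at 0.37". It reports 35 events for 80% power. The second step converts 35 events into patients, using a control event rate of 0.53, a control median survival of 1.3 years, a censoring rate of 0.1 (no unit given) and an average follow-up of 5 years. It ends: "Therefore, a total of 57 subjects were needed for the study".

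The article does not distinguish an enrolled number from an evaluable number, and it gives no reason for the two figures to differ.

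**The concern.** A trial should have one enrolment target, and here there are two. An enrolled-versus-evaluable distinction would not explain them, because the enrolled figure would then be the larger. Here the number to be enrolled (55) is smaller than the number said to be needed (57).

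The abstract is the most widely read statement of the sample size. A reader who takes 55 from it and 80% power from the sample size section combines two figures that do not belong together. The questions are which figure the calculation supports and how much power depends on the choice.

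**Working it through.** **Inputs**, all from the Sample size justification: two-sided alpha 0.05 (z = 1.960); beta 0.2 (z = 0.842); proportions 0.66 (nephrectomy groups pooled) and 0.34 (ICIs only); relative hazard 0.37; control event rate λ₀ = 0.53 per year; censoring rate c = 0.1; follow-up T = 5 years. The control rate and the control median agree: ln 2 / 1.3 = 0.533. Both values of λ₀ are carried through below.

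**Assumption.** The censoring rate is read as an annual exponential rate.

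**Step 1: events (Schoenfeld formula).**

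D = (1.960 + 0.842)² / [0.66 × 0.34 × (ln 0.37)²] = 35.38

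The article gives 35, so this step reproduces.

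**Step 2: probability that a patient's death is observed.**

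P = λ/(λ + c) × [1 − exp(−(λ + c)T)]

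- ICIs only, λ = 0.53: P₀ = (0.53/0.63) × [1 − exp(−3.15)] = 0.805
- Nephrectomy groups, λ = 0.53 × 0.37 = 0.196: P₁ = (0.196/0.296) × [1 − exp(−1.48)] = 0.512
- Weighted: 0.34 × 0.805 + 0.66 × 0.512 = 0.611

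With λ₀ = ln 2 / 1.3 the three values are 0.807, 0.514 and 0.613.

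**Step 3: patients.**

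N = 35 / 0.6114 = 57.2 (or 35 / 0.6132 = 57.1)

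This reproduces the article's 57.

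**Step 4: other readings of the inputs.** Changing one element at a time, with λ₀ = 0.53:

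| Reading | N for 35 events |
|---|---|
| As stated, censoring 0.1 per year | 57.2 |
| No censoring | 48.0 |
| Censoring of 10% in total over 5 years | 49.9 |
| Proportions 0.66 and 0.34 swapped | 49.6 |
| Equal split when converting events to patients | 53.2 |

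None of these gives 55.

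**Step 5: expected deaths and power at each target.** Expected deaths are d = N × P, and power is Φ[√(d × 0.66 × 0.34) × |ln 0.37| − 1.960].

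| N | λ₀ = 0.53: deaths, power | λ₀ = ln 2 / 1.3: deaths, power |
|---|---|---|
| 55 | 33.6, 78.0% | 33.7, 78.1% |
| 57 | 34.9, 79.4% | 34.9, 79.5% |

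Enrolling 55 instead of 57 costs about 1.2 expected deaths and 1.4 points of power.

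**The case against.** The strongest reply is that two patients hardly matter. That largely stands. A reader might infer from 55 that the trial is materially underpowered, but the figures do not support this. The loss is about 1.4 points, and 57 itself gives 79.4 to 79.5%, which is 80% only after rounding.

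The unit of the censoring rate is also open. Read as 10% in total over five years, 55 patients would give about 38.6 deaths and 83% power, and there would be no shortfall. That reading, however, gives N = 49.9 and not the article's 57. One route does come near 55: inflating 49.9 by 1/0.9 gives 55.5. It would count the same 10% twice, the article describes no such step, and it does not lead to 57.

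Other tempting inferences also fail:

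- *No allowance for losses.* The censoring rate is an allowance: without it 48 patients would suffice, so about 9 of the 57 are there because of it. Whether that covers the exclusions under Dropout criteria, Statistical analysis and Adherence with study protocol is a separate question.
- *Events wrongly rounded down.* Taking 35.38 as 35 gives 79.6% power, and 58 patients (58 × 0.6114 = 35.5 deaths) already reach 80%. This is immaterial.
- *Safety looks disturbed.* Looks at 25% and 50% fall at 13.75 and 27.5 patients for 55, or 14.25 and 28.5 for 57. The shift is at most one patient, and Interim analyses gives these fractions only as approximate.
- *The final analysis should be event-driven.* That is a design preference. The article's choice is not an error.

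The two conflicting totals remain, and none of these replies reconciles them.

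**Conclusion.** The point holds as an inconsistency in a basic design figure. The abstract's 55 contradicts the 57 of the Sample size justification, and the article's own inputs support 57. The consequence is small: about 78% power with about 34 expected deaths at 55, against 79 to 80% with about 35 at 57.

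The size of the shortfall rests on exponential survival, on the pooled 0.66/0.34 comparison used in the article's calculation, and on reading the censoring rate as annual. The last is an assumption, chosen because it reproduces the article's result. Differences of a tenth of a point between the two versions of the control rate carry no meaning.

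**What to change.** State 57 as the enrolment target in the abstract and wherever else the sample size appears. The description of power as 80% can then stand as a rounded figure.

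If 55 is the real target, say so in the Sample size justification and restate power as about 78% with about 34 expected deaths. In either case, give the unit of the censoring rate so that the calculation can be repeated without an assumption.

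The cost is a one-line correction, with no change to the design, conduct or analysis.

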**Discussion:**

This study is one of the few prospective randomized trials to evaluate the benefit of CN in the treatment of synchronous mRCC in the IO era. The SEVURO-CN trial will help identify the role and timing of CN, thereby rediscovering the value of CN.

**Trial registration:**

ClinicalTrials.gov, NCT05753839. Registered on 3 March 2023.

**Supplementary Information:**

The online version contains supplementary material available at 10.1186/s13063-024-08234-2.

## Background

Annually, over 75,000 individuals are newly diagnosed with renal cell carcinoma (RCC) in the USA, and its incidence is increasing [1]. Although the majority of RCC are diagnosed as localized cases, approximately one-third of patients have synchronous metastasis [2]. Nearly 14,000 cancer-specific deaths have been reported in the USA [1], with 5-year survival rates for metastatic renal cell carcinoma (mRCC) being quite low (0–20%), establishing it as a deadly disease [3–6].

Based on two randomized trials, cytoreductive nephrectomy (CN) was previously considered the standard treatment for the management of patients with mRCC with a good performance status [7, 8]. However, these studies were performed in the era of interferon therapy [7, 8], and dramatic advancements in systemic therapies have questioned the utility of CN. Two prospective randomized trials, CARMENA [9] and SURTIME [10], changed the standard first-line treatment for mRCC by downsizing the role of CN.

However, recently updated analyses of the CARMENA trial have suggested that some patients still benefit from CN [11]. Furthermore, the development of immune checkpoint inhibitors (ICIs) has revolutionized the treatment landscape [12], disrupting the treatment paradigm for mRCC and further complicating the definition of the role of CN. ICIs are now the standard of care for patients with intermediate- and poor-risk diseases. However, the CARMENA and SURTIME trials were performed in the tyrosine kinase inhibitor (TKI) era [13]; therefore, current clinical data on ICIs are limited. The role of CN in patients with high-risk localized tumors and favorable-to-intermediate-risk metastatic tumors falls into a gray zone [14]. Therefore, rather than a black-and-white approach, a combination of surgery and systemic therapy is likely to be beneficial for these patients [15].

The theoretical benefits of CN remain unclear, but the postulated mechanisms include the removal of the immunological sink, reduction in potential interaction between the primary tumor and its metastatic sites, and removal of possible de novo metastatic disease that stems from the renal primary [14, 16].

Two ongoing phase 3 randomized clinical trials (RCTs), PROBE (NCT04510597) and NORDICSUN (NCT03977571), are currently investigating the role of deferred versus no CN, and neither trial has included an upfront CN arm. Furthermore, no studies have been presented regarding the association between the analysis of clinical samples from the tumor tissue, blood, urine, and feces, and clinical parameters to develop biomarkers. Finally, a patient selection model for upfront CN in immuno-oncology (IO) era has never been presented.

### Objectives

The primary aim of this study is to investigate the role of CN in overall survival (OS). Our secondary aim is to investigate the role of CN in the progression-free survival (PFS), objective response rate (ORR), number of participants with treatment-related adverse events, and number of participants with surgical morbidity.

Furthermore, we will collect samples (tumor tissue, blood, urine, and feces) not only to explore the effects of CN in the tumor immune microenvironment (TIME) by analyzing genetic mutations and microbiome profiles but also to establish a biobank for future studies that search for biomarkers focusing on identifying survival outcomes, therapeutic responses, and patient selection.

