#### Group-specific criteria

Group A: Upfront CN: cytoreductive nephrectomy ± metastasectomy, followed by induction therapy with nivolumab plus ipilimumab, and maintenance therapy with nivolumab.

Group B: Deferred CN: cytoreductive nephrectomy ± metastasectomy after induction therapy with nivolumab plus ipilimumab, followed by maintenance therapy with nivolumab.

Group C: No surgery: induction therapy with nivolumab plus ipilimumab followed by maintenance therapy with nivolumab.

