### Study timeline

After completing the recruitment procedure, clinical and pathological data were collected (Table 1).

**Table 1 Tab1:** Clinical and pathological data

Clinical data				Pathological data
Baseline	Surgery-related	ICI therapy-related	Oncological outcome	
Age	OR note (including any intraoperative events)	Dosage	Overall survival	Pathological TNM staging
Sex	EBL	Cycle	Progression-free survival	Cell type
Height	Surgical morbidity (according to CDC)	Toxicities (graded by CTCAE v5.0)	Objective response rate (according to RECIST v1.1)	ISUP nuclear grade
Weight		Total administration periods		
BMI		Cause of discontinuation		
BSA				
KPS				
IMDC risk feature				
Clinical TNM staging				
Metastatic sites				

*BMI* body mass index, *BSA* body surface area, *CDC* Clavien–Dindo classification, *CTCAE* Common Terminology Criteria for Adverse Events, *EBL* estimated blood loss, *IMDC* International mRCC Database Consortium, *ISUP* International Society of Urologic Pathologists, *KPS* Karnofsky Performance Status, *OR* operating room, *RECIST* Response Evaluation Criteria for Solid Tumors

A flowchart of the study is shown in Fig. 1. Patients will be evaluated for eligibility for surgery. If they are not eligible for surgery, they will start ICI therapy (induction phase). Then, they will be assessed for whether they are eligible for surgery. If not, they will continue with ICI therapy (maintenance phase) (Group C). If they are eligible for surgery, they will be randomly allocated to the deferred CN group (Group B) or ICIs only. If they are eligible for surgery at the first visit, they will be randomly allocated to the upfront CN Group A (group A) or the deferred CN group (Group B). Patients will be randomly allocated in a 1:1 ratio using a computer-generated allocation sequence by a local project nurse. The randomization will be performed on an institutional basis to prevent bias.

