**Fig. 1 Fig1:**
[figure not shown]
Study flowchart. CN, cytoreductive nephrectomy; IMDC, International mRCC Database Consortium; Ipi, ipilimumab; mRCC, metastatic renal cell carcinoma; Nivo, nivolumab; KPS, Karnofsky performance status

Candidates for CN are patients with good performance status (Karnofsky performance status ≥ 80%) and less than three IMDC risk features and whose primary tumor could be surgically removed. Metastasectomy can be performed when the metastatic sites can be surgically removed. All patients eligible for ICI therapy will receive four cycles of intravenous nivolumab (3 mg/kg) plus ipilimumab (1 mg/kg) every 3 weeks as the induction phase, followed by a response evaluation. After the induction phase, intravenous nivolumab (3 mg/kg) will be administered 6 times every 2 weeks as the maintenance phase, followed by response evaluation. Nivolumab monotherapy will be maintained for a maximum of 2 years for those without adverse side effects. During ICI therapy, adverse events will be evaluated once per cycle. Patients will discontinue ICI therapy when they develop serious adverse events, including grade 3 or worse, according to the Common Terminology Criteria for Adverse Events version 5.0 (CTCAE v 5.0). In the upfront CN group, the induction phase will be within 6 weeks of surgery, whereas in the deferred CN group, surgery will be performed within 6 weeks of the induction phase. The study will be conducted over a period of 5 years.

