### Statistical analysis

Descriptive statistics will be used to assess clinicopathological characteristics. Mean values and standard deviation will be provided for continuous variables, whereas frequency and percentage distributions will be provided for categorical variables. Groups will be compared using the chi-square test for categorical variables and the Student’s *t*-test for continuous variables. The Kaplan–Meier and log-rank test method and log-rank test will be used to estimate and compare OS and PFS. Univariate and multivariate survival analyses will be conducted using the Cox proportional hazards model, which will provide hazard ratios (HRs) with 95% confidence intervals (CI). For subjects without endpoints or who violate the study protocol will be excluded. Statistical analysis will be performed using SPSS software (version 25.0; IBM, Armonk, NY) and R software [V.3.6.2 (http://www.R-project.org)]. The significance level will be set at *P* < 0.05, and all statistical tests will be two-sided.

Microbiome analyses will be conducted using 16S rRNA sequencing to determine the differences in alpha diversity among the three groups by calculating the Shannon, Chao1, and Simpson indices. Beta diversity will be generated using the weighted UniFrac distance and visualized using a principal component analysis plot. Between-group differences were analyzed using multivariate analysis of variance with permutation. Furthermore, subgroup analysis according to the number and location of metastasis will be performed.

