### Interim analyses

The data management and monitoring team monitors safety outcomes and provides recommendations regarding the continuation or premature termination of the trial. No interim analyses concerning efficacy are performed. We planned two interim statistical analyses on safety during the course of this study, after approximately 25% and 50% of the inclusion. The only stopping condition is based on safety. The decision to stop or continue is made by the trial team based on the advice of the data management and monitoring team. The risk of life-threatening immune-related adverse complications will be evaluated.

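### No stated endpoint measures severe harm on one scale in all three groups, so the total severe harm added by nephrectomy cannot be read from the planned counts

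*Protocol article*

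**What the plan says.** The Objectives section of the protocol article sets the role of CN as the secondary aim and lists two harm measures, "number of participants with treatment-related adverse events, and number of participants with surgical morbidity". The Methods part of the Abstract lists the same two.

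Table 1 (Study timeline) records them in different columns on different scales. The surgery column has "Surgical morbidity (according to CDC" (CDC is the Clavien-Dindo classification). The ICI column has "Toxicities (graded by CTCAE v5.0".

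The text after Fig. 1 gives the only stated schedule for adverse events: "During ICI therapy, adverse events will be evaluated once per cycle". It also fixes how close surgery is to drug treatment: "In the upfront CN group, the induction phase will be within 6 weeks of surgery, whereas in the deferred CN group, surgery will be performed". For the deferred group the limit is likewise 6 weeks, measured from induction.

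Under Group-specific criteria, "Group C: No surgery: induction therapy with nivolumab plus ipilimumab followed by maintenance therapy with nivolumab". The Study design section describes the trial as open-label. For the safety looks, the Interim analyses section names immune-related events only: "The risk of life-threatening immune-related adverse complications will be evaluated".

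**The concern.** The role of CN in harm can only be learned by comparing groups with and without CN. Of the two stated counts, one cannot be compared with Group C because nobody there is operated on. The other appears to be built around ICI toxicity. The two cannot simply be added: a participant may appear in both, and a grade on one scale is not a grade on the other.

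There is also a judgement of cause. Renal impairment, fever, or a lung, bowel or liver event near the operation could be put down to surgery or to the drugs. An unblinded investigator decides this in Groups A and B. In Group C the choice does not arise.

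At stake is a plain answer to how much severe harm CN adds. The Discussion says that CN should be considered by weighing benefits against risks. Benefit has a common measure, overall survival. Severe harm has none.

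**Working it through.** **Figures available.** The document states no adverse-event rate, no surgical-morbidity rate and no complication window, so there is no harm figure to reproduce. The sample-size figures concern overall survival and do not bear on this point.

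**Step 1: what each count can compare.**

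| Stated count | Scale (Table 1) | Stated assessment | Groups A and B | Group C |
|---|---|---|---|---|
| Treatment-related adverse events | CTCAE v5.0, listed for ICI toxicities | Once per cycle during ICI | Can score | Can score |
| Surgical morbidity | Clavien-Dindo | None stated | Can score | Zero by design |

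**Step 2: two readings of treatment-related.** The article does not define the term.

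- *ICI only.* Table 1, the per-cycle evaluation and the wording on the safety looks all point this way. Surgical events then fall outside the first count. A Group A participant whose surgical complication prevents ICI from starting would count as free of treatment-related events.
- *ICI and surgery.* Surgical events then belong in the first count, but Table 1 lists no CTCAE grade for them and the stated evaluation runs only during ICI cycles. Severity still cannot be compared across groups.

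Either reading leaves no common measure of severe harm.

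**Step 3: direction of misattribution (ICI-only reading).** Let *a* be the true proportion with ICI toxicity, assumed equal in all groups. Let *s* be the proportion with a surgical complication in a CN group, assumed independent of ICI toxicity. Let *r* be the share of participants with ICI toxicity whose counted events are all recorded as surgical. Let *q* be the share of participants with a surgical complication and no ICI toxicity whose complication is recorded as ICI-related.

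- First count in a CN group: a − a·r + (1 − a)·s·q. In Group C: a.
- Shift: (1 − a)·s·q − a·r.
- With a = 0.45 and s = 0.20: 0.11q − 0.45r, which is zero at r = 0.24q.
- With a = 0.45 and s = 0.10: 0.055q − 0.45r, which is zero at r = 0.12q.

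The document gives neither q nor r, so the sign is open.

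**Step 4: what the first count alone would not show.** With no misattribution (q = r = 0), the first count shows a difference of 0. Any harm in a CN group is 1 − (1 − a)(1 − s), so the excess over Group C is (1 − a)·s. All rates are assumptions.

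- a = 0.45, s = 0.10: any harm 1 − 0.55 × 0.90 = 50.5%, excess 5.5 points.
- a = 0.45, s = 0.20: any harm 1 − 0.55 × 0.80 = 56%, excess 11 points.
- Wider range, a from 0.3 to 0.7 and s from 0.1 to 0.4: from 0.3 × 0.1 = 3 points to 0.7 × 0.4 = 28 points.
- Without independence, at a = 0.45: from 0 (every surgical complication in someone who also has ICI toxicity) up to s (no overlap), that is 0–10 or 0–20 points.

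**Step 5: precision of a common count.** The sizing shares of 0.34 and 0.66 applied to 57 give about 19 and 38 participants. For 50% against 60% (a = 0.5, s = 0.2), the standard error is √(0.5·0.5/19 + 0.6·0.4/38) = 0.14 and two-sided power at 5% is about 11%. The result would be an estimate with a wide interval.

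**The case against.** The strongest reply is that the plan never excludes surgery from treatment-related events. CN is protocol treatment in Groups A and B, and Table 1 lists data to collect; it does not define endpoints. This stands: the ICI-only reading is an inference. It does not remove the point, because the other reading also leaves surgical events without a CTCAE grade.

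Other replies also stand in part. Using CTCAE for drug toxicity and Clavien-Dindo for operative complications is not an error. Rules on relatedness and complication windows commonly sit in a full protocol or analysis plan, so their absence here is no finding. No formal harm test is specified: the sentence "Groups will be compared using the chi-square test for categorical variables" sits with the description of clinicopathological characteristics. A count of any ICI toxicity or any surgical complication could be derived from the recorded data; what could not be derived is severe harm on one scale.

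A reader might infer three stronger things, none of which the document supports.

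- *The plan favours surgery.* Surgical morbidity is a listed endpoint on which only operated participants can score, so surgical harm is reported. Misattribution can also raise the first count in Groups A and B. The comparison misleads only if the first count is read alone as total harm, and nothing says it will be.
- *A large share of event time is open to re-attribution.* Over 30 weeks (12 induction, 12 maintenance, 6 around CN), an assumed 30-day window is 4.3/30 = 14% and a 90-day window 12.9/30 = 43%. But nivolumab may run to 2 years. Over 12 + 6 + 104 = 122 weeks the shares are 3.5% and 11%. These are also shares of time, not of events, and in Group A there is no ICI toxicity to re-attribute before the first dose.
- *The 5.5 to 11 points measure attribution bias.* They contain no re-attribution. They show only what a single count leaves out.

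**Conclusion.** The concern holds in a limited form. The secondary aim is the role of CN in harm, but the two stated counts cannot be combined on one severity scale, and one of them is zero by design in Group C. Events near surgery depend on an unblinded judgement of cause in Groups A and B only, which can distort the adverse-event comparison in either direction. The stated endpoints therefore do not give the total severe harm added by CN.

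The size cannot be computed from the document. The 5.5 to 11 points rest on assumed rates, equal ICI toxicity in all groups and independence. Surgical harm remains visible as its own endpoint, and neither the primary analysis nor the sample size is affected. This is a worthwhile, inexpensive improvement and does not undermine the trial.

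**What to change.** - **Endpoint** (Abstract, Methods; Objectives): add the proportion of participants with any grade 3 or higher adverse event of any cause by CTCAE v5.0, including surgical complications. This takes the judgement of cause out of the comparison.
- **Window**: collect it in all groups over a common window that includes the perioperative period, whether or not ICI is being given. In Group B the operation may fall up to 4 × 3 + 6 = 18 weeks after induction starts, so a shorter window would capture surgery in Group A and could miss it in Group B.
- **Clock**: follow the randomisations in the Study timeline section. Count A versus B from the first-visit randomisation and B versus C from the post-induction randomisation, each among the participants so randomised. Report non-randomised Group C patients separately. There is no randomised A versus C comparison, and a common count does not create one.
- **Table 1**: record a CTCAE grade beside the Clavien-Dindo grade for each surgical complication.
- **Breakdowns**: keep ICI toxicity and Clavien-Dindo morbidity as descriptive results. Make no formal comparison restricted to operated patients, because being operated on in Group B is decided after randomisation and those who progress or become unfit would drop out.

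The cost is a revision of endpoint wording, one extra grade per complication already recorded, and event collection outside ICI cycles where this is not already done. The downside is a little more coding and an all-cause rate that includes some disease-related events. Recruitment is planned to run to December 2027. Given the precision shown above, report the count as an estimate with its confidence interval.
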